### 2.9. Statistical Analysis Plan

Descriptive statistics will be presented on baseline characteristics of the two groups. Continuous variables reported as mean (standard deviation) or median (interquartile range), while categorical variables will be reported as frequencies and percentages.

The primary outcome, post-operative pain measured by VAS, will be compared between groups using an independent-samples *t*-test if normally distributed, or a Mann–Whitney U test if non-normally distributed.

Secondary outcomes will be analysed as follows:Post-operative analgesia requirements (oral morphine equivalents) will be compared using *t*-tests or Mann–Whitney U tests, depending on data distribution.Complication rates will be compared between groups using χ^2^ tests or Fisher’s exact tests where appropriate.Procedure duration and number of biopsy cores will be analysed using *t*-tests or non-parametric equivalents.

All statistical tests will be two-sided, with a significance level set at *p* < 0.05. Effect sizes with 95% confidence intervals will be reported for primary and secondary outcomes. Missing data will be handled using complete case analysis. Statistical analysis will be performed using SPSS (Version 29, Armonk, NY, USA).

In the event of significant missing data, a sensitivity analysis will be performed to assess the robustness of these findings.

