## 2. Patient and Methods

### 2.1. Study Design

This is a prospective, multicentre, randomised controlled trial (RCT) designed to evaluate the efficacy of PPNB in men undergoing TPPB under general anaesthesia. Participants will be recruited from three centres in Sydney, Australia: Chris O’Brien Lifehouse, Sydney Adventist Hospital, and Blacktown District Hospital.

The primary objective of this trial is to determine whether the addition of a periprostatic nerve block reduces post-operative pain, measured using a 10-point visual analogue scale (VAS) prior to discharge, in men undergoing transperineal prostate biopsy under general anaesthesia.

The secondary objectives are to evaluate whether the use of a periprostatic nerve block is associated with differences in complication rates compared to placebo, and to assess whether it reduces the requirement for post-operative analgesia.

This study has received ethical approval from the Sydney Local Health District Human Research Ethics Committee (2020/ETH03024) and has been registered with the Australian New Zealand Clinical Trials Registry (ACTRN12621001143819). All procedures will be performed in accordance with the National Statement on Ethical Conduct in Human Research (2018), Good Clinical Practice guidelines, and the principles of the Declaration of Helsinki. Trial conduct will be overseen by the principal investigator at each site, with central coordination by the chief investigator and support from a study coordinator.

At the study conclusion, a formal data analysis will be undertaken to obtain the result of this study. A schematic SPIRIT format of the study design is outlined in Table 1.

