### 2.4. Randomisation

After informed consent, participants will be randomised in a 1:1 ratio to receive either:

Intervention group: PPNB administered with 20 mL 1% lignocaine with 1:100,000 adrenaline (approved for use by the Therapeutic Goods Administration and listed on the Australian register of Therapeutic Goods (ARTG). The ARTG is a register of therapeutic goods that can be lawfully supplied in Australia), injected under ultrasound guidance immediately prior to biopsyControl group: placebo injection with 20 mL sterile 0.9% normal saline, injected under ultrasound guidance immediately prior to biopsy

The randomisation sequence will be computer generated using variable block sizes (2, 4 and 6); stratification will be by site. The allocation sequence will be prepared off-site by a trained study secretary, who will sequentially number and seal opaque envelopes. A box containing the required number of envelopes for use at each site will be made.

On the day of biopsy, a trained scout nurse will remove a sealed envelope from the box outside the operating theatre. The envelope will be opened, and the allocated injectate (PPNB or placebo) will be prepared in an unlabelled syringe of identical appearance. The scout nurse, who is not involved in outcome collection, will remain the only unblinded team member. Patients, surgeons, anaesthetists, and research staff collecting outcome data and performing analysis will remain blinded to allocation.

To reduce error, each envelope box will also contain a randomisation record, to be completed by the scout nurse at each location (Supplementary File S1). This document includes patient details, allocation, and solution preparation instructions, and will remain secured within the envelope box. A flowchart of instructions will also be affixed to each box to support adherence to protocol.

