These findings underscore that biopsy outcomes, such as patient-reported pain, may be influenced by operator-dependent factors such as experience, technical familiarity, and institutional practice patterns. Some degree of inter-operator and inter-centre variability is unavoidable and reflects pragmatic, real-world practice. In Australia, however, TPPB under general anaesthesia is the common and preferred approach. Thus, both trainees and consultant urologists in this study would have substantial exposure to and familiarity with the procedure, reducing the degree of operator variability compared to international settings where TPPB adoption remains inconsistent. Importantly, this enhances the external validity of the findings, although it may introduce additional variability in patient-reported outcomes.

Nevertheless, to date there is no high-quality evidence from randomised, double-blind, controlled trials examining PPNB (versus placebo) during TPPB under general anaesthesia. This multicentre trial is designed to address this evidence gap by providing blinded, controlled data on the effect of PPNB on early post-operative pain, analgesic use, and safety outcomes. However, the biggest challenge of this trial is that patient-reported pain is inherently subjective and may be influenced by individual pain thresholds, expectations, and peri-operative anxiety. Heterogeneity may also be introduced by the differences between centres in small variations in biopsy techniques.

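### Randomisation is stratified by site, but the primary VAS comparison leaves site out; if sites differ in mean pain, the t-test is conservative and precision is given away

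*Protocol article*

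**What the plan says.** Section 2.1: "Participants will be recruited from three centres in Sydney, Australia". Section 2.4: "participants will be randomised in a 1:1 ratio", with a sequence "computer generated using variable block sizes (2, 4 and 6); stratification will be by site". Section 3.1 counts the stratification as a strength because it reduces confounding by site.

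Section 2.9 then fixes the analysis. "The primary outcome, post-operative pain measured by VAS, will be compared between groups using an" independent-samples t-test, "or a Mann–Whitney U test if non-normally distributed". Oral morphine equivalents "will be compared using *t*-tests or Mann–Whitney U tests, depending on data distribution". Procedure duration and number of cores are handled the same way, and complications by χ² or Fisher's exact test. No analysis contains a site term or a stratified version of a test. The one sensitivity analysis named concerns missing data.

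The Discussion expects centres to differ: "Heterogeneity may also be introduced by the differences between centres in small variations in biopsy techniques". It gives no size.

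**The concern.** Blocking within site makes the arms nearly equal in number at each site, so differences in mean pain between sites largely cancel out of the treatment contrast. An unstratified t-test does not use this. It still counts the between-site variation as random error, so it reports a standard error larger than the real sampling variation of the estimate. The result is a test that rejects too rarely under the null, an interval that is too wide, and lower power than the design could give.

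The sample size leaves little slack: 22 per group is set for 80% power. Section 4 would also read a null result as a sign that the additional injection is not needed, so precision given away for nothing bears on how the trial will be read.

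**Working it through.** **Inputs from the protocol (Sections 2.1, 2.4, 2.7).** Three sites; 1:1 allocation; blocks of 2, 4 and 6 within site; difference 1.5; SD 1.75; two-sided α 0.05; 80% power; 22 per group evaluable (44 in total), 50 recruited.

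**Assumptions, because the documents give no figures.** Sites of 16/14/14 evaluable patients; site means at −g, 0 and +g, so adjacent sites differ by g and the extremes by 2g; normal outcomes. Section 2.7 does not say whether 1.75 is a within-site or an overall SD, so both readings are shown.

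**Step 1: the plan's own figure.** n = 2 × (1.960 + 0.842)² × (1.75/1.5)² = 2 × 7.85 × 1.361 = 21.4, so 22 per group. This reproduces the plan. The exact noncentral-t power at 22 per group is 79.3%.

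**Step 2: what the unadjusted standard error contains.** The between-site variance is V = (30/44)g² − (2g/44)² = 0.680g². If 1.75 is the within-site SD, the t-test reports roughly √[(1.75² + V) × 2/22]:

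- g = 0.5: V = 0.170, SE ≈ √(3.232 × 0.0909) = 0.542
- g = 1.0: V = 0.680, SE ≈ √(3.742 × 0.0909) = 0.583
- g = 1.5: V = 1.530, SE ≈ √(4.592 × 0.0909) = 0.646

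With V removed, the SE is about √(3.0625 × 0.0909) = 0.528 at every gap.

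**Step 3: simulation.** 8,000 trials per setting, Monte Carlo error about ±1 point on power. The unadjusted two-sample t-test (42 df) is compared with a linear model with arm and site indicators (40 df).

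*1.75 as within-site SD*

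| Gap g | Unadjusted: mean reported SE / true sampling SD | Type I error, unadjusted / adjusted | Power, unadjusted / adjusted |
|---|---|---|---|
| 0 | 0.525 / 0.530 | 5.3% / 5.4% | 79.2% / 79.1% |
| 0.5 | 0.541 / 0.528 | 4.3% / 4.9% | 77.7% / 79.0% |
| 1.0 | 0.583 / 0.525 | 3.0% / 5.0% | 71.7% / 78.3% |
| 1.5 | 0.648 / 0.544 | 1.8% / 5.1% | 63.6% / 78.8% |

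*1.75 as overall SD (within-site variance = 1.75² − V)*

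| Gap g | Unadjusted: mean reported SE / true sampling SD | Type I error, unadjusted / adjusted | Power, unadjusted / adjusted |
|---|---|---|---|
| 0.5 | 0.527 / 0.513 | 4.4% / 4.8% | 79.8% / 81.3% |
| 1.0 | 0.527 / 0.468 | 2.5% / 4.8% | 81.7% / 88.3% |
| 1.5 | 0.531 / 0.383 | 0.6% / 4.8% | 87.0% / 97.9% |

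The power difference between the two analyses at g = 0.5, 1.0 and 1.5 is therefore about 1, 7 and 15 points on the first reading, and about 1.5, 7 and 11 points on the second.

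**Step 4: interval width.** The adjusted model's mean reported SE on the first reading is 0.526. The unadjusted interval is wider by 0.541/0.526 = 1.03, 0.583/0.526 = 1.11 and 0.648/0.526 = 1.23, that is by about 3%, 11% and 23%.

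**Step 5: uneven sites.** With 24/12/8 patients and 1.75 within site, power at the three gaps is 77.7/72.7/65.5% unadjusted and 79.3/79.0/79.4% adjusted: the same pattern.

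**The case against.** The strongest reply concerns size. A pooled SD entered in a two-group calculation without a site term is naturally read as the SD over all patients in an arm, which already includes any site variation. On that reading the unadjusted test keeps the planned 80%. The larger gaps are also demanding: g = 1.0 puts the extreme sites 2 points apart, more than the 1.5-point treatment effect, and makes site about 18% of total variance (0.680/3.742) when 1.75 is the within-site SD. The Discussion calls the variations in technique small and argues that operators in Australia are familiar with the procedure. At g = 0.5 the cost is about 1 point of power. And the error is on the safe side, so a positive result is not called into question.

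All of this stands as a limit on size. It does not remove the mismatch: on either reading the unadjusted t-test is conservative once sites differ, and with no site difference adding site costs nothing detectable (79.2% against 79.1%).

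A second objection also stands. Only the t-test on normal data was simulated. VAS is bounded at zero and the Introduction puts post-procedural pain at 30–50% of patients, so the rank-test branch may well be used. No figure is available for it or for the secondary outcomes; there the case for including site rests on the same design logic and not on a calculation.

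**Conclusion.** The point holds as a modest improvement that is practically free. Section 2.9 names the tests, so this is a stated choice that does not match the stated randomisation. If site means differ, the t-test's SE is overstated, its interval too wide and its type I error below 5%. The loss relative to a site-adjusted analysis is negligible at a gap of 0.5 points and material from about 1 point, under assumed site sizes and gaps.

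Three stronger readings are tempting and are not supported:

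- That the trial is underpowered because site is ignored. This follows only if 1.75 is the within-site SD and the gaps are large; the documents establish neither.
- That the result could be biased or falsely positive. The estimate is unbiased, and the error rate moves down, not up.
- That every test must be stratified, or that baseline covariates such as age and prostate volume should be added. Complications may be too few to stratify by three sites, and nothing in the documents shows that those covariates predict VAS.

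**What to change.** Before unblinding, replace the primary comparison in Section 2.9 with a linear model of VAS on arm and site, and report the site-adjusted mean difference with its 95% CI. If a rank test is used, make it the site-stratified version (van Elteren). Treat the continuous secondary outcomes (oral morphine equivalents, procedure duration, number of cores) in the same way. Leave complications unstratified if events are sparse.

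It would also help to state in Section 2.7 whether 1.75 is a within-site or an overall SD, because this decides whether the planned power depends on the adjustment.

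The cost is a sentence or two in the plan and 2 degrees of freedom (40 instead of 42 with 44 evaluable patients). Site is known for every patient from the randomisation, so no new data are needed.

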## 3. Discussion

Analgesia in prostate biopsy is an underappreciated but important clinical aspect affecting patients, influencing pre-procedural anxiety and post-procedural discomfort and analgesic needs, even if performed under general anaesthesia. While TPPB has increasingly replaced the transrectal approach due to better prostate sampling and reduced risk of sepsis, which is reflected in the European Association of Urology Guidelines’ strong recommendation [17], it is more painful than the traditional transrectal approach. In the contemporary era of active surveillance, where men may undergo repeat biopsies, optimisation of post-procedural discomfort is important not only to reduce immediate morbidity but also to support long-term adherence to surveillance protocols.

Analgesic strategies in prostate biopsy historically focus on transrectal approach, where PPNB has strong evidence from systematic reviews and meta-analyses supporting its efficacy, with or without adjuncts such as intrarectal local analgesia, in reducing pain compared to placebo or no injection [18,19]. A recent RCT comparing perineal nerve block to PPNB in TPPB under local anaesthesia showed that perineal nerve block had lower pain scores during and at 1 h post-procedure [20]. This suggests that the optimal analgesia for TPPB differs from the transrectal approach.

There is also important heterogeneity in real-world TPPB practice that warrants consideration when interpreting this study. Variability exists not only in biopsy technique, but also in operator experience and training pathways. In a prospective study of naïve trainees, different technical approaches were associated with differences in procedural efficiency and cancer detection in specific subgroups, highlighting the influence of operator learning curves and technique selection on outcomes [21]. Furthermore, contemporary international survey data demonstrates substantial variability in trainee exposure to TPPB, with fewer than half of urology trainees reporting hands-on experience and marked differences between countries and institutions [22]. This heterogeneity extends to procedural independence, with proficiency closely linked to procedural volume.

These findings underscore that biopsy outcomes, such as patient-reported pain, may be influenced by operator-dependent factors such as experience, technical familiarity, and institutional practice patterns. Some degree of inter-operator and inter-centre variability is unavoidable and reflects pragmatic, real-world practice. In Australia, however, TPPB under general anaesthesia is the common and preferred approach. Thus, both trainees and consultant urologists in this study would have substantial exposure to and familiarity with the procedure, reducing the degree of operator variability compared to international settings where TPPB adoption remains inconsistent. Importantly, this enhances the external validity of the findings, although it may introduce additional variability in patient-reported outcomes.

Nevertheless, to date there is no high-quality evidence from randomised, double-blind, controlled trials examining PPNB (versus placebo) during TPPB under general anaesthesia. This multicentre trial is designed to address this evidence gap by providing blinded, controlled data on the effect of PPNB on early post-operative pain, analgesic use, and safety outcomes. However, the biggest challenge of this trial is that patient-reported pain is inherently subjective and may be influenced by individual pain thresholds, expectations, and peri-operative anxiety. Heterogeneity may also be introduced by the differences between centres in small variations in biopsy techniques.

### 3.1. Strengths

This multicentre, double-blinded, randomised controlled design is a key methodological strength, minimising selection and detection bias. Stratified randomisation by site also reduces site-specific confounding. The use of concealed allocations preserves the blinding of patients, surgeons, anaesthetists and outcome assessors. The protocolised PPNB technique and standardised outcome measurement strengthens the study’s reproducibility. Objective endpoints are achieved via standard conversion to oral morphine equivalents. The pragmatic inclusion of three tertiary centres also further strengthens the external validity within Australia.

### 3.2. Limitations

However, there are some limitations inherent to this study. The modest sample size, powered to detect a clinical difference in early post-operative pain, may limit ability to detect smaller differences in secondary outcomes. Pain is inherently subjective and influenced by patient pain thresholds; in addition, peri-operative anxiety and recovery room factors may introduce variability. Variations in biopsy template, number of cores and subtle inter-operator technique differences across centres may introduce heterogeneity, although this reflects real-world practice.

## 4. Conclusions

Regardless of direction, the results of this trial will offer robust, clinically relevant evidence for practitioners and may inform future guidelines on analgesic practice in TPPB. If PPNB demonstrates meaningful benefit, it could be considered as a routine adjunct. Conversely, a null finding would suggest that additional injections are unnecessary, streamlining procedural workflows. In either case, this trial may encourage further exploration of block strategies (e.g., perineal nerve block, pudendal block) and analgesia optimisation in prostate biopsy practice.

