# Periprostatic Nerve Block During Transperineal Prostate Biopsy Under General Anaesthesia: Protocol for a Multicentre Pilot Randomised Controlled Trial

**DOI:** 10.3390/cancers18081251

**Published:** 2026-04-15

**Keywords:** anaesthesia, periprostatic nerve block, post-operative pain, prostate biopsy, prostate cancer, randomised controlled trial, visual analogue scale

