### 2.7. Sample Size

The primary outcome of interest is the between-group difference in the post-procedure VAS scores between the intervention (PPNB) and placebo injection. A meta-analysis of transrectal prostate biopsies demonstrated that PPNB was associated with a considerable reduction in post-procedural pain, with a pooled standardised mean difference of −1.27 (95% CI −1.72 to −0.82) compared with placebo [14]. Although this suggests a large effect size, the analysis also reported significant heterogeneity (I^2^ = 92%), reflecting variability across trials. A separate review of acute pain interventions reported that the minimum clinically important difference ranged from 0.4 to 4.0, with a median of 1.7 on a 10-point VAS [15].

On this basis, the sample size calculation assumed a between-group difference of 1.5 on the VAS, with a pooled standard deviation of 1.75, corresponding to a large effect size (Cohen’s *d* = 0.86). Using a two-sided α of 0.05 and 80% power, the required sample size is 22 patients per group. Allowing for dropout, a total of 50 patients will be recruited (25 per group). The sample size calculation was performed using G*Power v3.1.9.6 [16].

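### The Conclusions read any null result as suggesting the injections are unnecessary, without tying that reading to the planned 95% confidence interval

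*Protocol article*

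**What the plan says.** The Conclusions (Section 4) state in advance how either outcome will be read. They open with "Regardless of direction, the results of this trial will offer robust, clinically relevant evidence for practitioners", and for the negative case continue: "Conversely, a null finding would suggest that additional injections are unnecessary, streamlining procedural workflows".

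The design behind those sentences is as follows.
- The title reads "Protocol for a Multicentre Pilot Randomised Controlled Trial".
- Section 2.7 reports, from a review of acute pain interventions, that "the minimum clinically important difference ranged from 0.4 to 4.0, with a median of 1.7 on a 10-point VAS". It then says that "the sample size calculation assumed a between-group difference of 1.5 on the VAS, with a pooled standard deviation of 1.75", and "Using a two-sided α of 0.05 and 80% power, the required sample size is 22 patients per group". Recruitment is set at 50, or 25 per arm.
- Section 2.9 compares VAS scores by a t-test or a Mann–Whitney test, two-sided at 0.05. It also commits to effect sizes with 95% confidence intervals. It does not say what an interval must show before a null is read as absence of need.
- Section 3.2 admits that the modest sample may miss smaller differences, but confines that caveat to the secondary outcomes.

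**The concern.** A non-significant test of difference says that zero is compatible with the data. It does not say that a worthwhile benefit is incompatible with them. The sentence in the Conclusions covers every null alike: one whose interval lies well below 1.5 points and one whose interval contains both zero and 1.5. Only the first says anything against the benefit the trial was designed to find. Because Section 3.2 leaves the primary outcome without a caveat, nothing in the article warns the reader of this.

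At stake is the use made of a negative result. The same paragraph expects the trial to inform guidelines. A block with a moderate real benefit could be set aside on the strength of an inconclusive pilot.

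**Working it through.** **Inputs.** Design difference 1.5, SD 1.75, two-sided alpha 0.05, power 80%, 22 per arm required, 25 per arm recruited, and cited important differences of 0.4 to 4.0 with median 1.7 (all Section 2.7); 1:1 allocation (Section 2.4); test and intervals (Section 2.9). Scores are modelled as normal and compared by t-test.

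**1. The plan's own figure.** n = 2(1.960 + 0.842)² × 1.75² / 1.5² = 21.4, so 22 per arm. The stated number reproduces. Exact t-test power is 79.3% at 22, 81.1% at 23 and 84.4% at 25.

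**2. Expected half-width of the 95% interval.** t(0.975, 2n−2) × SD × √(2/n):
- 22 per arm: 2.018 × 1.75 × 0.3015 = 1.06
- 25 per arm: 2.011 × 1.75 × 0.2828 = 1.00

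**3. Observed results that are null yet compatible with 1.5.** The observed benefit must be below the half-width (non-significant) and above 1.5 minus the half-width (1.5 inside the interval):
- 22 per arm: 0.44 to 1.06
- 25 per arm: 0.50 to 1.00

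At the top of these ranges the upper limit is about twice the half-width, 2.1 or 2.0. Both exceed the cited median of 1.7.

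**4. How frequently this happens.** One million simulated trials per scenario, SD 1.75, shown as 22 / 25 per arm:

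| True benefit | Null trials | Null trials with 1.5 inside the interval | Both, as a share of all trials |
|---|---|---|---|
| 0 | 95% / 95% | 19% / 14% | 18% / 13% |
| 0.4 | 89% / 88% | 41% / 33% | 36% / 29% |
| 1.0 | 54% / 49% | 72% / 66% | 39% / 33% |
| 1.5 | 21% / 16% | 88% / 84% | 18% / 13% |

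**5. What a null can rule out.** If the true effect is zero, the interval excludes 1.5 in 79% / 84% of trials. The number per arm that excludes a benefit m with 80% power when the truth is zero is 2(1.960 + 0.842)² × 1.75² / m²:
- m = 1.5: 22
- m = 1.0: 49
- m = 0.4: 301

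The trial is large enough for the first and too small for the other two.

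**6. Sensitivity to the SD.** The documents give no SD other than 1.75. If it were 2.5 (an assumption), the half-width would be 1.52 / 1.42. Then 51% / 45% of null trials would still include 1.5 with a true effect of zero, and 87% / 86% with a true benefit of 1.0.

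**The case against.** The strongest reply is that this is one hedged, forward-looking sentence. It speaks of suggesting, not showing, and the paragraph elsewhere says only that results may inform guidelines and may encourage further work. It contains no p-value rule and changes no test, estimate or sample size. Section 2.9 promises the intervals that a careful reader needs, and an interpretation margin could sit in an analysis plan that is not shown. All of this stands, and it limits the severity. It does not cure the sentence, which is a published statement about every null and makes no reference to the interval.

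A reader might infer that a trial of 50 can say nothing useful after a null. The figures do not support that: with no true effect, about four trials in five exclude the 1.5-point design difference.

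A reader might also infer that null results will usually leave 1.5 open. That depends on the true effect and the SD. At SD 1.75 it holds for most nulls when the true benefit is 1.0 or 1.5, but for fewer than one in five when it is zero. A null when the true benefit is 1.5 is the ordinary type II error of a design with about 80% power, not an added defect.

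**Conclusion.** The point holds in a limited form. The Conclusions attach one reading to all null results, and this document does not make that reading depend on the planned interval. At the plan's SD a null can rule out 1.5 and often will if the block does nothing. It cannot be expected to rule out smaller benefits within the range of important differences that the plan cites: power is 46% / 51% for a true 1.0 points and 11% / 12% for 0.4 (22 / 25 per arm). The claim of robust evidence in either direction is too strong for a pilot of this size.

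The sizes rest on SD 1.75, normal scores and a t-test. A Mann–Whitney test would have slightly less power under normality (about 77% / 83% for 1.5, taking its relative efficiency as 0.955), and a larger SD makes a null less informative. Severity is minor to moderate: the interpretation needs correcting, while design and analysis are untouched.

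**What to change.** Replace the sentence on null findings with a reading based on the 95% confidence interval of the mean VAS difference, reported whichever test is used:
- If the result is null and the interval excludes the 1.5-point design difference, conclude that a benefit of that size is unlikely, and add that smaller benefits are not ruled out.
- If the interval includes both 0 and 1.5, call the result inconclusive.

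Soften the words on injections being unnecessary and on robustness, and describe the result as pilot evidence. Extend the sample-size limitation in Section 3.2 to the primary outcome.

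The cost is wording only: no patients, procedures or tests change. The downside is that the claim available after a null result becomes weaker. Section 2.7 does not present 1.5 as the smallest worthwhile difference, so excluding it answers only the question the trial was sized for. Making the change before results are known avoids choosing the interpretation afterwards.
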